### Who will take informed consent? {26a}

A list of eligible participants and their spouses is generated from examining patient medical histories from the First Affiliated Hospital of Dalian Medical University. BZ and ZL are responsible for recruitment and screening of the eligible participants. LP will complete study enrollment along with obtaining informed consent. Solicitation to eligible participants who meet the established study criteria will be made through phone calls or during routine check-ups. Participants reached over the phone will be invited to the hospital for a physical examination, review the study details, address any questions, and sign the consent form. No later than 1 week after the consent form is signed, will the baseline measurements be taken, and further at-home instructions be provided. Consent will be collected using a short form provided in Simplified Chinese (or in other languages upon request). The form includes a description of the study, reasonably foreseeable risks or discomfort to the participant, and the rights of the participant, including withdrawal of participation at any time. The form may be signed via signature or thumb print. If necessary, legally authorized representatives may also provide consent. Oral interpretation of the consent form may be provided for illiterate participants. Translators involved in consent taking will also be asked to sign the form. A copy of the form will be provided (paper and/or electronically) to the participant upon signage for the participant to keep as a record.

### Additional consent provisions for collection and use of participant data and biological specimens {26b}

On the consent form, participants are asked if their data can be used should they choose to withdraw from the trial. Participants are also asked for permission for the research team to share relevant data with personnel from the associated universities taking part in the research or from regulatory authorities, where relevant. The trial does not involve collecting biological specimen for storage.

## Interventions

### Explanation for the choice of comparators {6b}

The PD intervention group is compared with the PD control group and a healthy control (HC) group. The PD control group is composed of participants diagnosed with PD and who meet the inclusion criteria. This PD control group is instructed to maintain the participants’ prescribed medication and care documented at the time of baseline assessment including any form of deep brain stimulation, if applicable. Any deviation from what was recorded at the time of taking baseline assessments are recorded during assessments and included when analyzing the data.

The second control group, the HCs, is composed of participants who meet the HC group inclusion criteria. This group predominantly consists of healthy spouses of the PD participants and individuals who share similar demographics to the participants diagnosed with PD. Measurements from the HCs are necessary because they serve as a normal, non-pathological benchmark, which has not been recorded before with this specific demographic and type of study paradigm. Furthermore, since spouses typically have similar lifestyles as their partners the measurements taken may help reduce the uncontrollable deviations due to dietary habits, living conditions, and environmental factors. HCs are asked to continue normal routine and must report any major deviations from baseline assessment routine (e.g., new medication to treat non-neurological illnesses that may affect motor movement or major injuries like head trauma). These deviations are noted for data analysis.

The neuronal activities of generating motor movement or processing a rhythmic external cue each should separately elicit measurable neuronal activation. However, when combined, a sensorimotor integration effect occurs such that motor movement is the result of a rhythmic external cue. Thus, the use of the HC and PD controls is to examine how movement coupled with an external sensory cue (a rhythmic auditory stimulus and in this study, music with rich rhythmic contents) impacts motor synchronization and control in PD.

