### Eligibility criteria {10}

Potential participants will be recruited from the Neurology Department of the First Affiliated Hospital of Dalian Medical University in China. Only individuals who meet the inclusion criteria will be invited to participate in the study.

There will be two populations participating in this study: one will be patients diagnosed with PD with intervention and the other without. A group of healthy participants will be recruited to serve as healthy controls (HC) that will provide the baseline assessment data to gage the severity of PDs in the patient populations.

The following are the inclusion criteria for participants with PD recruitment:
Aged 40–80 years old, both genders, and right-handed;Clinical diagnosis of idiopathic PD according to the 2015 Movement Disorder Society (MDS) Clinical Diagnostic Criteria for Parkinson’s Disease;Rated as stage I to II on the Hoehn and Yahr scale;Score greater than 21 points on the Montreal Cognitive Assessment (MoCA);Maintain a stable dosing of anti-PD or deep-brain stimulation (DBS) treatment throughout the duration of the study;Able to travel to and participate in the data collection process.

Exclusion criteria for participants with PD recruitments include:
Individuals who do not meet the inclusion criteria;Presence of significant hearing impairments;Extensive previous musical training;A history of any other neurological condition (i.e., Alzheimer’s disease, epilepsy, stroke) or psychiatric disorders (i.e., major depression, psychoses).

The HC group will consist of subjects recruited from hospital staff and students as well as students and faculty members from Dalian University of Technology. In addition, participants’ spouses will also be invited to participate. The HC group must have the following qualities to be included:
Aged 40–80 years older, both genders, and right-handed.

HC will be excluded along the same criteria that was established for the PD recruitment.

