### Strategies to improve adherence to interventions {11c}

Participants’ primary caregivers are asked to monitor and, if needed, record completion of sessions using a smartphone with video and audio recording capabilities. The videos will be collected weekly either digitally through a secure cloud server or transferred from the phone if participant is available to come to the hospital on a weekly basis. Participants who do not have caregivers may be provided with a phone ring stand to help with recording themselves, if needed. In addition, a phone with video and audio recording capabilities is provided for participants who do not have one. These videos will be reviewed by a research assistant who is not involved in data collection or enrollment. For the intervention group, videos are scored separately for adherence and accuracy. Accuracy is determined by matching the time sequence of the song to that of the one used during the assessment. The HC and the control arm’s videos are scored on a binary adherence score. These scores are manually inputted into a designated spreadsheet and updated in the database weekly.

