### Outcomes {12}

The primary outcome measurements of this study are the following:
Improvement or preservation of SFT and continuous finger tapping (CFT) performances from baseline measurements for intervention group.Preserved or improved the Unified Parkinson’s Disease Rating Scale (UPDRS) scores from baselines measurements for intervention group in comparison to control arm.Reduced HbO_2_ levels in prefrontal cortex from baseline measurements for intervention group. Preserved or improved n-back task scores from baseline measurements for intervention group in comparison to control arm.Preserved or improved Montreal Cognitive Assessment (MoCA) scores from baseline measurements for intervention group in comparison to control arm.

Secondary outcome measurements of the study include:
Preserved motor control performances, UPDRS scores, HbO_2_ levels, n-back task scores and MoCA scores from baseline measurements in healthy control group.Preserved or aggravated motor control performances, UPDRS scores, HbO_2_ levels, n-back task scores, and MoCA scores from baseline measurements in PD control group.

These outcomes are determined by analyzing the differences between participants’ pre-, 4-week (during), 8-week (post), and 12-week (retention), neuroimaging, neurophysiological, and SFT performance scores as well as compared with the data from the control arms. Individual and grouped averaged measurements are examined.

Music-based therapies often report beneficial and positive results; however, little is known about how music improves neuronal activity and connectivity in individuals with neurological disease. The primary outcome measurements of this protocol: SFT and CFT performances, HbO2, UPDRS scores, n-back, and MoCA scores act as assessments to quantify the effects of a music-based synchronous finger tapping training in individuals with PD. The trial’s outcomes may be used to enhance current clinical care of patients with PD by supplementing or augmenting current PD treatments with music-based exercises. There are currently no anticipated harmful outcomes because the use of fNIRS has been shown to be clinically safe and feasible. Consequently, this study was determined to be a low-risk intervention by the participating hospital’s Ethics Committee and the Steering Committee.

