### Concealment mechanism {16b}

Once the consent form is received, a computer-generated random number from 1 to 210 will be assigned to that participant. Each number from 1 to 210 will be assigned a random group type: PD intervention, PD control, or HC. HCs can only be assigned numbers assigned an HC group type. For the numbers randomly allotted for PD participants, the computer-generated random number assignment will be set such that results in a 1:1 ratio, stratified by gender and PD staged I and staged II determined by the Hoehn and Yahr scale. The participant’s number will become the identifier for the participant’s collected data for data analysis. Once all participants have been enrolled and assigned, the list of which participants were distributed among the groups will be kept in an opaque, sealed envelope. Upon completion of consent, randomization, and baseline data collection, the participant will receive an opaque and sealed envelope, associated with their randomized number. The package will provide further at-home instructions as a physical copy, contact information for additional questions, and how to access a digital copy of their assigned group’s instructions. Verbal instructions, additional resources, and training for at-home tasks will be provided to participants and caregivers. Access to video instructions for at-home tasks is also provided as a supplement.

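### Spouses can be both healthy controls and caregivers trained in the home task; no rule separates the roles or puts the spouse's baseline before that training

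*Protocol article*

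**What the plan says.** **Who the healthy controls are.** Explanation for the choice of comparators {6b}: "This group predominantly consists of healthy spouses of the PD participants"; the sentence goes on to name a second source, people demographically similar to the patients. Eligibility criteria {10} gives a different emphasis: "The HC group will consist of subjects recruited from hospital staff and students as well as students and faculty members from Dalian University of Technology", after which participants' "spouses will also be invited to participate". The consent section {26a} lists eligible patients together with their spouses, and Recruitment {15} also invites spouses.

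**What they are asked to do.** Section {6b}: "HCs are asked to continue normal routine". Major departures from that routine must be reported; the examples are new medication and serious injury.

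**What caregivers do.** Concealment mechanism {16b}: "training for at-home tasks will be provided to participants and caregivers". Implementation {16c} repeats this. Under {11c}, "primary caregivers are asked to monitor and, if needed, record completion of sessions". The intervention description {11a} sets one session a day for 8 weeks.

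**How the healthy data are used.** The abstract compares the PD groups with the healthy group's baseline. Outcomes {12} makes stability of the healthy group a secondary outcome; its list of measures ends with MoCA "scores from baseline measurements in healthy control group". The statistical section on finger tapping and neuropsychological assessments compares the three groups by t test.

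**The concern.** In a couple, the person who helps with the home task may well be the spouse, and the protocol deliberately recruits that spouse as a healthy control. If the partner is in the intervention arm, the spouse can be shown the task, hear the music and see paced tapping repeatedly, and then be tested on finger tapping with fNIRS at weeks 4, 8 and 12. Spouses of PD control participants have no such exposure. The healthy group would then mix exposed and unexposed people, with exposure set by the partner's randomised arm.

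The planned data, as described, do not show who is who. A drift in the healthy group could be ordinary retest behaviour or the result of exposure, and the two could not be told apart. If the spouse is enrolled after the partner, the exposure could even precede the spouse's own baseline, which is the reference for both PD groups.

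**Working it through.** **1. Are the roles separated?** Sections {10}, {26a}, {6b} and {15} bring spouses in as healthy controls. Sections {16b}, {16c} and {11c} bring caregivers into training and monitoring. The healthy-control criteria in {10} do not mention caregiving, and no section records who holds both roles. The reporting duty in {6b} could in principle catch it, but its examples would not prompt a spouse to report helping with the task.

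**2. Is the order fixed?** Section {26a} puts baseline within 1 week of consent, and {16b} hands over the envelope after consent, randomisation and baseline. Both are written for each participant's own sequence. Neither links a spouse's baseline to the partner's training.

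**3. How many could be exposed?** The protocol gives no figure. Inputs:
- 70 healthy controls (Sample size {14});
- PD participants allocated 1:1 ({16a}), so about half of the spouses have a partner in the intervention arm, if spouses come evenly from both arms;
- s = share of healthy controls who are spouses, assumed 50–100%;
- c = share of those spouses who act as caregiver, assumed 25–100%.

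Exposed number = 70 × s × 0.5 × c:

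| s | c = 25% | c = 50% | c = 75% | c = 100% |
|---|---|---|---|---|
| 50% | 4.4 | 8.8 | 13.1 | 17.5 |
| 75% | 6.6 | 13.1 | 19.7 | 26.2 |
| 100% | 8.8 | 17.5 | 26.2 | 35.0 |

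The ends are 0.5 × 0.5 × 0.25 = 6% (about 4 people) and 1 × 0.5 × 1 = 50% (35 people).

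**4. What would that do to the healthy mean change?** If exposure shifts an exposed person's change by e on average, the group mean shifts by (exposed share) × e, that is 0.06e to 0.50e. The protocol gives no value for e.

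For scale only, take a treatment effect of 0.5 SD. This is an assumption, since {14} states no effect size or SD. It does fit the stated sample size: 63 per group gives about 80% power at two-sided 0.05, and 63 / 0.9 = 70. If exposed spouses gained 25–100% of 0.5 SD:
- exposed share 12.5%, gain 25%: 0.5 × 0.125 × 0.25 = 0.016 SD;
- exposed share 25%, gain 50%: 0.5 × 0.25 × 0.50 = 0.06 SD;
- exposed share 50%, gain 100%: 0.5 × 0.50 × 1 = 0.25 SD.

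**5. Which comparisons are touched?** PD intervention against PD control uses no healthy data and is unchanged. Healthy change from baseline and any post-baseline comparison with the healthy group are touched. The healthy baseline is touched only if it is taken after the partner's training.

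**The case against.** The case against has weight.

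- **Most healthy controls need not be spouses.** The sentence in {6b} names two sources together, and {10} lists staff, students and faculty first. This stands. The two sections do not fix the spouse share, and 50% is not a firm floor: at s = 25% the exposed number is 2.2–8.8.
- **The caregiver need not be the spouse.** No section says so, {11c} foresees participants without caregivers, and {11a} has participants film themselves, with help optional. Patients at Hoehn and Yahr stage I–II may need little help. This also stands, and is why c is an assumption.
- **Watching is not doing.** The intervention is the patient's own tapping to music, whereas the assessment is key tapping to a visual cue. The melody was chosen because it is already familiar. So e may be close to zero. The protocol, however, collects nothing that would show this.
- **The healthy group is mainly a baseline reference.** This is true of the abstract, but {12} also makes its stability over time a secondary outcome.
- **The order within a couple is scheduling detail that an article may omit.** This is fair, and patients and spouses are listed together in {26a}. A late spouse baseline is therefore a possibility left open, not something the protocol plans.
- **The healthy group may have a home task of its own.** Section {11c} scores its videos for adherence, which sits badly with normal routine in {6b}. This blurs the line between exposed and unexposed controls and is itself something to reconcile.

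A reader might infer that many or most healthy controls will be treated in effect. The documents do not support that: neither the spouse share nor the caregiver overlap is stated, and training or monitoring is not practice.

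**Conclusion.** The protocol allows one person to be a trained caregiver in the intervention arm and a healthy control, does not identify such people, and does not protect their baseline. That follows from the text without any assumption.

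The size does not follow from the text. About 4–35 of 70 (6–50%) rests on assumed spouse and caregiver shares; the upper end requires every healthy control to be a spouse and every spouse of an intervention participant to act as caregiver. The resulting bias is that share times an unknown, possibly small, effect.

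The point concerns the healthy reference data only. It should not be read as a threat to the randomised PD comparison. It merits a correction because the links are hard to reconstruct later and a baseline taken too late cannot be repaired.

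**What to change.** 1. In {6b} and {16b}, require a spouse's own baseline to be completed before the partner's envelope is opened and the couple is trained.
2. Record for each healthy control the linked PD participant, if any, and whether he or she acts as that participant's caregiver.
3. Keep all healthy controls in the main healthy analysis. Add a sensitivity analysis of week 4–12 change that leaves out caregiver spouses of intervention participants, and show those spouses separately.
4. Reconcile normal routine in {6b} with the scoring of healthy-control videos in {11c}, and state what those videos record. Align {6b} and {10} on where healthy controls come from.

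The cost is some visit ordering, two recorded fields and one extra analysis on fewer people: about 35–66 of 70 before attrition (70 − 35 and 70 − 4), under the assumptions above. Removing every spouse of an intervention participant from the main healthy analysis would go further than needed, because it would discard the lifestyle matching that {6b} gives as the reason for recruiting spouses.

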### Intervention description {11a}

After the baseline measurements, participants in the intervention arm will be trained to do a rhythmic auditory synchronous finger tapping (SFT) intervention task at the hospital and asked to practice at home for a total of 25 min split between two 10-min sets with a 5-min break between the sets every day for 8 weeks. During training sessions participants must listen to the instrumental of a pre-selected well-known Chinese melody, i.e., 荷塘月色 (pinyin: “hé táng yuè sè”; English: “Moonlight over the Lotus Pond” by Phoenix Legend) whose melody duration is 259 s. This song was selected for its strong beat and familiarity to most of the participants. Participants must follow the beats of the melody and tap their right index finger simultaneously to the beats. The training session will be conducted once daily after patients have taken their medication. They are also instructed to take a video recording of themselves with their smartphones for the entire duration of the training. They may also solicit the help of their primary caregivers for the recording. This is for the purpose of monitoring protocol compliance.

### Criteria for discontinuing or modifying allocated interventions {11b}

Participants may stop participation at any time during weeks 0–12 due to various reasons including failure to meet inclusion criteria or inability to continue at-home intervention.

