**Fig. 1 Fig1:**
[figure not shown]
Expected trial plan. Not included in the diagram are excluded participants that may stop participation at any time during weeks 0–12 due to various reasons including failure to meet inclusion criteria or inability to continue at-home intervention. The intervention tasks are 25 min total, with two 10-min sets with a 5-min break between each set

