**Fig. 3 Fig3:**

Schematic of experimental paradigm. BR, baseline rest; SFT, synchronous finger tapping; CFT, continuous finger tapping. In the SFT task, visual stimuli will appear at three different rates 1000 ms, 1500 ms, and 2000 ms respectively

Three neuropsychological assessments will be employed for measuring the therapeutic effects of the music therapy on the disease. The Unified Parkinson’s Disease Rating Scale (UPDRS), n-back task, and Montreal Cognitive Assessment (MoCA) will also be measured at baseline, 4, 8, and 12 weeks.

Three neuropsychological assessments will be employed for measuring the therapeutic effects of the music therapy on the disease. The Unified Parkinson’s Disease Rating Scale (UPDRS), n-back task, and Montreal Cognitive Assessment (MoCA) will also be measured at baseline, 4, 8, and 12 weeks.

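### The wording on leaving the study lets PD participants be stopped after randomisation for no longer meeting an inclusion criterion, and one such criterion (MoCA) is also a primary outcome

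*Protocol article*

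**What the plan says.** Section 11b of the protocol article, on discontinuing or modifying the allocated intervention, states: "Participants may stop participation at any time during weeks 0–12 due to various reasons including failure to meet inclusion criteria". The Fig. 1 legend uses the same period and reason, and describes these people as "excluded participants that may stop participation at any time during weeks 0–12".

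The eligibility section (10) lists for PD participants "Score greater than 21 points on the Montreal Cognitive Assessment (MoCA", together with Hoehn and Yahr stage I to II and stable anti-PD or DBS treatment for the length of the study.

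The outcomes section (12) names as a primary outcome "Preserved or improved Montreal Cognitive Assessment (MoCA) scores from baseline measurements for intervention group in comparison to control arm". The assessment section, below Fig. 3, says that the "n-back task, and Montreal Cognitive Assessment (MoCA) will also be measured at baseline, 4, 8, and 12 weeks".

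Section 20a starts the analysis once the retained participants have finished week 12, and section 20c removes missing data. On treatment changes, the comparator section (6b) says: "Any deviation from what was recorded at the time of taking baseline assessments are recorded during assessments and included when analyzing the data".

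**The concern.** Weeks 0–12 run beyond consent, allocation and baseline. If failing an inclusion criterion is a ground for leaving throughout that time, the criteria can be read as continuing conditions. A participant who enters with a MoCA of 22 and scores 21 at week 4 then fails one, and the failure is itself a value of a primary outcome.

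The trial asks whether function is preserved with training and, in the PD control arm, whether it is "Preserved or aggravated motor control performances, UPDRS scores" and so on. Loss that depends on decline bears directly on that question. It takes out more of whichever arm declines more, makes those who remain look better preserved, and uses up the attrition allowance. The week 8 and week 12 measurements of every other outcome in those participants are lost too.

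**Working it through.** **Step 1. The text side by side.**

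| Element | Where | What it fixes |
|---|---|---|
| Reason for leaving | 11b; Fig. 1 legend | Failing an inclusion criterion, weeks 0–12 |
| Criterion | Eligibility (10), PD list | MoCA above 21 |
| Outcome | Outcomes (12) | MoCA, intervention against control, primary |
| Timing | Assessment section, below Fig. 3 | Baseline, weeks 4, 8, 12 |
| Analysis | 20a, 20c | Retained participants; missing data removed |

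No section confines the inclusion criteria to screening or exempts MoCA afterwards. No section orders a follow-up MoCA to be compared with 21 either. The combination permits removal for decline and does not mandate it.

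**Step 2. Size, by simulation.** There is no figure in the plan to reproduce, because the protocol gives no MoCA mean, SD, reliability or expected change. From the documents: entry above 21, visits at weeks 4, 8 and 12, 70 participants per group, 10% attrition. Assumed: everything else.

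- True score T ~ N(μ, 2²), with μ = 24, 25 or 26.
- Baseline b = round(T + e), with e ~ N(0, σ²) and σ = 1.0 or 1.5. Scores are held to 0–30, and entry requires b > 21.
- Individual change to week 12: D ~ N(d, 1), with d = 0 in the intervention arm and d = −1 in controls.
- Follow-up score Y_k = round(T + D·k/3 + e_k), for k = 1, 2, 3 (weeks 4, 8, 12).
- Stopped if Y_1 ≤ 21 or Y_2 ≤ 21. Week 12 is not a trigger, because by then the last score has been collected.
- Difference = mean(Y_3 − b) in the intervention arm minus the same in controls. Shrinkage = 1 − (difference in those not stopped ÷ difference in everyone).

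| μ | σ | Stopped, intervention | Stopped, control | Difference, everyone | Difference, not stopped | Shrinkage |
|---|---|---|---|---|---|---|
| 24 | 1.0 | 11.2% | 17.7% | 0.996 | 0.948 | 4.8% |
| 24 | 1.5 | 17.0% | 23.7% | 0.992 | 0.939 | 5.4% |
| 25 | 1.0 | 5.9% | 10.1% | 0.987 | 0.956 | 3.2% |
| 25 | 1.5 | 9.9% | 14.6% | 0.978 | 0.941 | 3.8% |
| 26 | 1.0 | 2.7% | 4.9% | 0.966 | 0.948 | 1.8% |
| 26 | 1.5 | 5.1% | 8.0% | 0.954 | 0.930 | 2.5% |

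**Step 3. Reading the table.** Controls are stopped more often in every row. The intervention arm, with no average decline, still loses 3–17%, through measurement error and individual variation near the limit. The 10% allowance is 0.10 × 70 = 7 people per arm. It is exceeded in 6 of the 12 arm-scenarios (two intervention, four control). The bias in the MoCA contrast is small and towards no difference.

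**The case against.** The strongest reply is that no such rule exists. The sentence in 11b is permissive and lists reasons why people leave; it does not tell staff to re-screen. The eligibility section invites only those who meet the criteria, which points to a judgement at entry. Some criteria continue by nature: stable treatment, and being able to travel to and take part in data collection. Failing the latter is ordinary attrition. Ineligibility found late, around baseline, is another innocent meaning. Hoehn and Yahr stage is not among the scheduled follow-up assessments. A condensed article may also leave detailed withdrawal rules to the full protocol.

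Most of this stands, and it limits the point to what the wording allows. It does not remove the point, because the text is not confined to those narrower meanings. The legend classes these people as excluded, and at least one inclusion criterion does run through the study. The concern is with a sentence the article states, not with detail it leaves out.

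A reader might go further in four ways that the documents do not support:

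- *That participants will be removed when MoCA falls to 21 or below.* No section says so.
- *That the MoCA difference would shrink by 7–21%.* The same model gives that only if scores of 21 or below at week 12, already collected at the last visit, are also discarded. Ending follow-up cannot do that.
- *That the randomised comparison is destroyed.* The illustrated bias is small and concerns MoCA, one of several primary outcomes. The sample size section rests on HbO2, for which no bias is shown.
- *That section 6b contradicts 11b on treatment changes.* Recording and analysing a deviation is compatible with allowing a participant to leave. The passages need reconciling, but they can both hold.

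**Conclusion.** The point holds as a defect of wording. Sections 10, 11b and 12 and the Fig. 1 legend together permit follow-up of a randomised PD participant to end because a primary outcome declined, and sections 20a and 20c offer no way back into the analysis for the visits missed. Hoehn and Yahr stage raises the same issue if it is re-rated. The MoCA limit is listed for PD participants, so the problem lies in the randomised comparison and not in the healthy control group.

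On the assumptions above, the more visible cost is unequal loss between arms, which can by itself exceed the planned attrition; the 2–5% bias in MoCA is secondary. These figures assume that the limit is applied to everyone at weeks 4 and 8 and that controls lose 1 point by week 12. Neither assumption comes from the documents. If staff never apply the criteria after entry, the loss is nil. I would rate this a moderate wording correction, not a condition for going ahead.

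**What to change.** 1. In sections 10 and 11b and in the Fig. 1 legend, state that inclusion criteria are judged once, before randomisation.
2. In 11b and the legend, remove failure to meet inclusion criteria as a reason for leaving the study after randomisation.
3. State that randomised participants are still assessed at weeks 4, 8 and 12 whatever their later MoCA or Hoehn and Yahr stage.
4. Reconcile sections 10, 6b, 11b and 11d on what a change of treatment means for study participation and analysis. How treatment is managed is a clinical matter and is not addressed here.

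The cost is an amendment to wording. The visits concerned are already in the schedule, and clinical care is unaffected.
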